## Abstract

**Background:**

The evidence on the effects of metformin and insulin in type 2 diabetes patients on quality of life, patient satisfaction, and cardiovascular outcomes is unclear.

**Methods:**

The Copenhagen Insulin and Metformin Therapy (CIMT) trial is an investigator-initiated multicentre, randomised, placebo-controlled trial with a 2 × 3 factorial design conducted at eight hospitals in Denmark. Participants with type 2 diabetes were randomised to metformin (n = 206) versus placebo (n = 206); in combination with open-label biphasic insulin aspart one to three times daily (n = 137) versus insulin aspart three times daily in combination with insulin detemir once daily (n = 138) versus insulin detemir once daily (n = 137).

We present a detailed description of the methodology and statistical analysis of the clinical CIMT outcomes including a detailed description of tests of the assumptions behind the statistical analyses. The outcomes are quality of life (Short Form Health Survey (SF-36)), Diabetes Medication Satisfaction Questionnaire, and Insulin Treatment Satisfaction Questionnaire (assessed at entry and 18 months after randomisation) and cardiovascular outcomes including time to a composite of either myocardial infarction, stroke, peripheral amputation, coronary revascularisation, peripheral revascularisation, or death.

**Discussions:**

This statistical analysis plan ensure the highest possible quality of the subsequent post-hoc analyses.

**Trial registration:**

The protocol was approved by the Regional Committee on Biomedical Research Ethics (H-D-2007-112), the Danish Medicines Agency (EudraCT: 2007-006665-33 CIMT), and **registered** within ClinicalTrials.gov (NCT00657943, 8^th^ of April 2008).

## Background

1

The Copenhagen Insulin and Metformin Therapy (CIMT) trial is an investigator-initiated multicentre, randomised, placebo-controlled superiority trial with a 2 × 3 factorial design [1]. The CIMT trial evaluated the effect of an 18-month treatment with metformin versus placebo and simultaneously the effect of three insulin analogue regimens on the progression of mean carotid intima media thickness in patients with type 2 diabetes [1]. The CIMT trial was conducted from May 2008 to December 2012 and the trial results in relation to changes in carotid intima media thickness have been reported [2,3]. Metformin in combination with insulin did not reduce the carotid intima media thickness [2]; nor did the three insulin regimens [3]. Multiple exploratory analyses have since been carried out, but the prespecified patient-centred clinical outcomes quality of life, patient satisfaction, and time to a number of clinical and cardiovascular outcomes have not yet been reported [1,[4], [5], [6]].

One previous systematic review assessed the effects of adding metformin to insulin in people with type 2 diabetes [7]. We identified only three trials assessing the influence of metformin versus placebo on health-related quality of life or well-being [[7], [8], [9], [10]]. All three included trials were at high risk of bias, and all three trials had a shorter duration and included fewer participants than the CIMT trial [7]. None of the included trials reported significant differences regarding the patient-reported outcomes [[7], [8], [9], [10]]. Only Douek et al. [8] reported results of quality of life assessments in a way suitable for a meta-analysis, and it was therefore not possible to meta-analyse quality of life as an outcome [7]. The reporting of cardiovascular complications for the comparison of combining metformin with insulin compared with insulin monotherapy in people with type 2 diabetes was infrequent, and when meta-analyses could be performed, the data were sparse and effect estimates were non-significant [7].

Here, we describe a detailed statistical analysis plan of post-hoc analyses assessing the effects of metformin in addition to insulin and the effect of three different insulin regimens on patient-reported outcomes and cardiovascular complications in the CIMT trial.

## Methods

2

The methodology of the CIMT trial have previously been published [1]. The CIMT trial participant inclusion criteria were: type 2 diabetes; age >30 years; body-mass index >25 kg/m^2^; HbA1c ≥ 7.5% (58 mmol/mol); and treatment with oral glucose-lowering drugs for at least one year and/or insulin treatment for at least three months [1]. After a screening visit, participants were centrally randomised at the Copenhagen Trial Unit according to the 2 × 3 factorial design. Participants were randomised 1:1:1 to treatment with one of three insulin analogue regimens and in a factorial way randomised 1:1 to treatment with metformin versus placebo (Fig. 1). Randomisation was stratified by age >65 years (yes/no), insulin treatment at trial entry (yes/no), and treatment at Steno Diabetes Center (yes/no) [1]. The insulin treatment was open-labelled, whereas participants, investigators, and medical staff were blinded to the metformin and placebo intervention (numbered identical containers) [1].

**Fig. 1 fig1:**
[figure not shown]
**–** A study scheme of the factorial designed trial, where participants are ranodmised into both factors. Thus, each participant is allocated in both Factor 1 and Factor 2, and receives a combination of the two treatment schemes.

The protocol was approved by the Regional Committee on Biomedical Research Ethics (H-D-2007-112) and the Danish Medicines Agency (EudraCT: 2007-006665-33 CIMT), registered within ClinicalTrials.gov (NCT00657943), and conducted in accordance with The Declaration of Helsinki and guidelines for Good Clinical Practice. Informed consent was obtained from each participant enrolled in the trial.

The design of the CIMT trial and the influence of metformin and insulin on the primary outcomes have previously been reported [2,3]. Here we report the detailed statistical analysis plans for evaluating the effects of these intervention on the patient-centred outcomes quality of life, patient satisfaction, and cardiovascular outcomes.

We plan on reporting the results of these outcomes in two separate papers: one comparing metformin versus placebo comparison and one comparing the three insulin analogue regiments.

## Outcomes

3

### Quality of life and patient satisfaction

3.1

•Short Form Health Survey (SF-36) [11]. SF-36 is questionnaire and a general assessment of quality of life measures. Both a physical component score and a mental health component score are reported [11].•Insulin Treatment Satisfaction Questionnaire (ITSQ) [12].•Diabetes Medication Satisfaction Questionnaire (Diab-Medsat) [13].

These continuous outcomes were assessed at 18 months after randomisation [1].

### Cardiovascular outcomes

3.2

•Time to myocardial infarction, stroke, peripheral amputation, coronary revascularisation, peripheral revascularisation, or death [1].•Time to myocardial infarction, stroke, peripheral amputation, or death [1].•Time to cardiovascular mortality [1].

The cardiovascular outcomes were assessed during the full observation period from randomisation of each patient into the trial and until June 11th, 2013 [1].

The outcome assessors and the participants were blinded to metformin versus placebo but not to the three insulin regimens [1]. We used the Danish Central Civil Register and the National Patient Register to obtain data on the cardiovascular outcomes [1].

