### Time to myocardial infarction, stroke, peripheral amputation, coronary revascularisation, peripheral revascularisation, or death

4.4

We consider a 29% risk of experiencing one or more of the following outcomes: non-fatal myocardial infarction, stroke, peripheral amputation, coronary revascularisation, peripheral revascularisation, or death in the placebo group [25], an alpha of 0.001, and a hazard ratio reduction of 30%. For the metformin versus placebo comparison, we will only have 9.0% power to confirm or reject a hazard ratio reduction of 30%. For each of the three pairwise insulin comparisons, we estimate that we will only have 4.5% power to confirm or reject a hazard ratio reduction of 30%.

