## Limitations

14

The statistical analysis plan also has limitations. First, the primary outcome of the CIMT trial was an non-validated surrogate outcome [1], and the analyses of the patient-centred outcomes described in the present statistical analysis plan should therefore be considered exploratory. Second, the power estimations of the cardiovascular outcomes showed that we do not have sufficient data to confirm or reject realistic intervention effects [15], so the results of the cardiovascular outcome will only be reported in the supplementary material. Third, this statistical analysis plan has been developed long after data accrual was stopped. However, the plan was developed and agreed upon without knowledge of the intervention effects or specific data.

We plan on a subsequent 10-year follow-up study of the cardiovascular outcomes, assessed using similar methodology as described in this statistical analysis plan. This would compensate for the low power regarding the cardiovascular outcomes because of only 18 months follow-up in 412 patients, we plan to prolong the follow-up for the participants after end of the trial. This would raise the power of our analyses of cardiovascular outcomes, but risk confounding by changes to anti-diabetic treatment after stop of the CIMT interventions.

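### Cardiovascular follow-up is given as randomisation to June 2013 in one section and as 18 months in another; the assumed risks are tied to neither, and the power figures use the placebo risk in both arms.

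*Protocol article*

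**What the plan says.** All references are to the protocol article.

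- Section 3.2 (Cardiovascular outcomes): events are "assessed during the full observation period from randomisation of each patient into the trial and until June 11th, 2013".
- Section 14 (Limitations) speaks of "low power regarding the cardiovascular outcomes because of only 18 months follow-up in 412 patients". It presents follow-up beyond the end of the trial as a future extension, and names confounding from treatment changes after the interventions stop as a risk of that extension only.
- Section 1 (Background): the trial "evaluated the effect of an 18-month treatment with metformin versus placebo", and "The CIMT trial was conducted from May 2008 to December 2012".
- Section 4.4: "We consider a 29% risk of experiencing one or more of the following outcomes" (this is the placebo-group risk), with "an alpha of 0.001, and a hazard ratio reduction of 30" per cent. For metformin versus placebo, "we will only have 9.0% power to confirm or reject a hazard ratio reduction of 30" per cent; for each insulin pair the figure is 4.5%. Sections 4.5 and 4.6 do the same with placebo risks of 12.5% (power 2% and 1.2%) and 3.8% (power almost 0% and 0%). None of the three risks is given a period.
- Section 8.3 plans Cox regression without naming a window. Section 8.6 lists splitting the observation period among the options to consider if log-log plots suggest non-proportional hazards, and gives no cut point.

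**The concern.** The two statements of follow-up cannot both describe the same analysis. A hazard ratio over 18 months compares the arms while they were on trial treatment. A hazard ratio to June 2013 compares them over that time plus a period after the interventions stopped. Readers, including the systematic reviewers whom section 12 names as users, need to know which one they have.

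The power figures depend on the same choice. A risk of 29% means one event rate if it accrues over 18 months and a much lower one if it accrues over several years. Without a period, the expected number of events in the analysed window cannot be worked out.

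The power arithmetic also has a smaller fault of its own. It assumes a 30% lower hazard in one arm, yet the stated figures appear to count events as if both arms had the placebo risk.

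**Working it through.** **1. Length of follow-up.** From May 2008 to 11 June 2013 is about 61 months. A participant who completed 18 months of treatment by December 2012 was randomised by about the end of June 2011, and so has about 23.4 months to the cut-off. The post-treatment part of each participant's potential follow-up is therefore:

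- latest entry: (23.4 − 18)/23.4 = 23%
- earliest entry: (61.3 − 18)/61.3 = 71%
- uniform entry over that period (assumed; accrual dates are not given): mean (23.4 + 61.3)/2 ≈ 42.4 months, share (42.4 − 18)/42.4 = 57.5%

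The share exceeds one half once mean follow-up exceeds 36 months.

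**2. Reproducing the stated power.** Schoenfeld's formula with 1:1 allocation is power = Φ(|ln HR| × √E / 2 − z), where E is the number of events. Here ln 0.70 = −0.3567, and z = 3.2905 for two-sided alpha 0.001 (the sidedness is not stated). With the placebo risk in both arms, E = 412 × 0.29 = 119.5, and power = Φ(0.3567 × 10.93/2 − 3.2905) = Φ(−1.341) = 9.0%, as stated. For an insulin pair, E = 274 × 0.29 = 79.5 gives 4.5%, as stated.

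**3. Using the plan's own hazard ratio.** Under proportional hazards the active-arm risk is 1 − (1 − placebo risk)^0.70. For 29% this is 1 − 0.71^0.70 = 0.213. Then E = 206 × (0.29 + 0.213) = 103.7 and power = Φ(−1.474) = 7.0%.

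| Outcome (placebo risk) | Comparison | Stated | Placebo risk in both arms | Lower active-arm risk |
|---|---|---|---|---|
| Six components (29%) | Metformin | 9.0% | 9.0% (119.5 events) | 7.0% (103.7) |
| | Insulin pair | 4.5% | 4.4% (79.5) | 3.5% (68.9) |
| Four components (12.5%) | Metformin | 2% | 2.2% (51.5) | 1.8% (44.1) |
| | Insulin pair | 1.2% | 1.2% (34.3) | 1.0% (29.4) |
| Cardiovascular death (3.8%) | Metformin | almost 0% | 0.5% (15.7) | 0.4% (13.3) |
| | Insulin pair | 0% | 0.3% (10.4) | 0.3% (8.9) |

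The 4.4% in the second row is 4.45% before rounding. The stated 2% is too coarse to tell 2.2% from 1.8%; the 9.0%, 4.5% and 1.2% figures identify the method. Other methods with the lower active-arm risk do not give 9.0%: Freedman gives 6.8%, two proportions 6.7%, and one-sided Schoenfeld 10.1%.

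**4. Effect of the missing period.** Six-component outcome, metformin versus placebo, exponential hazards, lower active-arm risk:

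| 29% is the risk over | Followed 18 months | Followed 42.4 months, HR 0.70 throughout | Followed 42.4 months, HR 0.70 to month 18, then 1 |
|---|---|---|---|
| 18 months | 7.0% | 22.7% | 1.1% |
| 42.4 months | 2.0% | 7.0% | 0.5% |
| 60 months | 1.2% | 4.2% | 0.4% |
| 96 months | 0.7% | 2.1% | 0.3% |

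Example for 22.7%: placebo risk 1 − 0.71^(42.4/18) = 0.554, active-arm risk 0.431, E = 206 × 0.985 = 202.9. The last column uses an average HR of (18 × 0.70 + 24.4 × 1)/42.4 = 0.87. The four periods in the rows, and the loss of effect at month 18, are illustrations and not figures from the plan.

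**The case against.** Section 3.2 is the operative outcome definition and is clear; section 14 is commentary, and an analyst would follow section 3.2. Comparing all randomised participants to a common registry cut-off is a legitimate treatment-policy analysis. The period of the assumed risks may be given in the cited source or the full protocol. Section 8.6 already contemplates splitting the observation period. Moving from 9.0% to 7.0% changes no decision, because power is inadequate either way and the plan itself says so, calls the outcomes exploratory and sends them to the supplement.

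Most of this stands, and it is why the point is minor. It does not remove the contradiction. Nor does it supply the missing acknowledgement that the present window already contains post-treatment time. The split in section 8.6 is conditional on a visual check that is weak with few events, and its cut point would be chosen with the data in view, which the plan says it wants to avoid.

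Three stronger readings are tempting, and the document does not support them:

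- *The stated power is too high overall.* This does not follow. If 29% is an 18-month risk and the effect persists to June 2013, power is about 22.7% and the stated 9.0% is too low.
- *Proportional hazards must fail in the long window.* That holds only if the effect changes when treatment stops. The document gives no post-treatment effect and does not describe what participants took after 18 months.
- *More than half of follow-up is known to be off treatment.* It is possible, and about 58% under uniform accrual, but accrual dates are not given.

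**Conclusion.** The contradiction between sections 3.2 and 14 is real. On the plan's own dates, any participant who completed treatment within the trial has at least about 23 months to the cut-off, so an analysis to June 2013 includes time after treatment. This rests on taking December 2012 as the end of trial treatment. The risks are tied to neither window, so power for the actual analysis is undetermined: 0.3% to 22.7% for the six-component metformin comparison over the scenarios shown.

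Independently of the window, and taking the risks as applying to whatever follow-up is analysed, the stated powers are modestly too high because the assumed benefit was left out of the event count. The size is 2 percentage points at most, assuming Schoenfeld's formula and a two-sided alpha. Severity is minor: no scenario makes these outcomes well powered.

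**What to change.** 1. Reconcile sections 3.2 and 14 on one window. If it is June 2013, correct the 18-month statement in section 14 and say there that the present hazard ratio already includes post-treatment time, not only the future 10-year study.
2. Keep the overall hazard ratio as the primary result. Add a pre-specified supplementary split at 18 months, with a hazard ratio before and after, in place of the open cut point in section 8.6.
3. State the period to which the 29%, 12.5% and 3.8% risks apply and the expected follow-up. Restate power for the chosen window with the lower active-arm risk, and say whether alpha is two-sided.

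The cost is wording, a short recalculation and one extra supplementary analysis; by the document's account the registry data run to June 2013 and so cover both periods. The drawback of the split is few events in each period, so its estimates will be imprecise and should be read as descriptive.

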## Sample size and power considerations

4

Based on the sample size calculation in relation to the primary outcomes of the trial (change in mean intima media thickness of the common carotid arteries), we planned to include a total of 950 patients in the trial [1]. However, the trial was stopped due the end of the financing grant after the inclusion of a total of 412 participants [2,3]. For this factorial trial, this means that there is a comparison on 206 participants on metformin versus 206 participants on placebo and another comparison of three groups on different insulin regimens each including 137, 137, and 138 participants.

To increase the interpretability of the trial results and decrease the risks of random errors [14], we present power estimations for all planned outcomes [15]. We originally adjusted our threshold for statistical significance (the alpha value used in the sample size estimations) to 0.01 because of the multiple comparisons [1]. To take into account that the CIMT trial was stopped early (approximately halfway), we will now use an alpha value of 0.001 for the power estimations [14]. The following power estimations are based on the total 412 randomised participants for the metformin versus placebo comparison and a total of 274 randomised participants for each of the three pairwise insulin comparisons.

### Short Form Health Survey (SF-36)

4.1

We consider 4 points as the minimal clinically relevant difference for SF-36 [14,[16], [17], [18], [19], [20], [21]], an alpha of 0.001, and a standard deviation (SD) of 9.5 points [12]. For the metformin versus placebo comparison, we will have a power of 83.0% to confirm or reject a 4-point increase on the SF-36. For each of the three pairwise insulin comparisons, we will have a power of 56.3% to confirm or reject a 4-point increase on the SF-36.

### Insulin Treatment Satisfaction Questionnaire (ITSQ)

4.2

We consider 4 points as the minimal clinically relevant difference for ITSQ [14,20], an alpha of 0.001, and a standard deviation (SD) of 9 points [22]. For the metformin versus placebo comparison, we will have a power of 88.3% to confirm or reject a 4-point increase on the ITSQ. For each of the three pairwise insulin comparisons, we will have a power of 63.7% to confirm or reject a 4-point increase on the ITSQ.

### Diabetes Medication Satisfaction Questionnaire (Diab-Medsat)

4.3

We consider 4 points as the minimal clinically relevant difference for Diab-Medsat [14,20,23], an alpha of 0.001, and a standard deviation (SD) of 9 points [24]. For the metformin versus placebo comparison, we will have a power of 88.3% to confirm or reject a 4-point increase on the Diab-Medsat. For each of the three pairwise insulin comparisons, we will have a power of 63.7% to confirm or reject a 4-point increase on the Diab-Medsat.

### Time to myocardial infarction, stroke, peripheral amputation, coronary revascularisation, peripheral revascularisation, or death

4.4

We consider a 29% risk of experiencing one or more of the following outcomes: non-fatal myocardial infarction, stroke, peripheral amputation, coronary revascularisation, peripheral revascularisation, or death in the placebo group [25], an alpha of 0.001, and a hazard ratio reduction of 30%. For the metformin versus placebo comparison, we will only have 9.0% power to confirm or reject a hazard ratio reduction of 30%. For each of the three pairwise insulin comparisons, we estimate that we will only have 4.5% power to confirm or reject a hazard ratio reduction of 30%.

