### Time to the first of the following clinical outcomes myocardial infarction, stroke, peripheral amputation, or death

4.5

We consider a 12.5% risk of experiencing one or more of the following outcomes: non-fatal myocardial infarction, stroke, peripheral amputation, or death in the placebo group [25], an alpha of 0.001, and a hazard ratio reduction of 30%. For the metformin versus placebo comparison, we will only have 2% power to confirm or reject a hazard ratio reduction of 30%. For each of the three pairwise insulin comparisons, we estimate that we will only have 1.2% power to confirm or reject a hazard ratio reduction of 30%.

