### Time to cardiovascular death

4.6

We consider a 3.8% risk of experiencing death from cardiovascular disease in the placebo group [25], an alpha of 0.001, and a hazard ratio reduction of 30%. For the metformin versus placebo comparison, we will have almost 0% power to confirm or reject a hazard ratio reduction of 30%. For each of the three pairwise insulin comparisons, we estimate that we will have 0% power to confirm or reject a hazard ratio reduction of 30%.

We plan to present the results of these three cardiovascular outcomes in the Supplemental material because of the low statistical power.

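### The power figures for the first cardiovascular composite (9.0% and 4.5%) fit the placebo-group risk applied to both arms; the plan's own inputs give about 7.0% and 3.5%

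*Protocol article*

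**What the plan says.** Section 4 of the protocol article sets common inputs for all power figures. On the significance level it says "we will now use an alpha value of 0.001 for the power estimations". For the metformin question the number analysed is the "total 412 randomised participants for the metformin versus placebo comparison", which means 206 per arm. The insulin regimens are compared two at a time, with "a total of 274 randomised participants for each of the three pairwise insulin comparisons", which means 137 per arm.

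Section 4.4 (six-component composite) takes a 29% risk, assigned explicitly to the placebo group, and a 30% reduction in the hazard. For metformin versus placebo it concludes that "we will only have 9.0% power to confirm or reject a hazard ratio reduction of 30" per cent. For the insulin pairs, "we estimate that we will only have 4.5% power to confirm or reject a hazard ratio reduction of 30" per cent.

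Section 4.5 (four-component composite) follows the same pattern with a placebo-group risk of 12.5%. It states 2% for metformin and, for the insulin pairs, "we estimate that we will only have 1.2% power to confirm or reject a hazard ratio reduction of 30" per cent. Section 4.6 (cardiovascular death) uses 3.8% and states almost 0% for metformin; for the insulin pairs, "we estimate that we will have 0% power to confirm or reject a hazard ratio reduction of 30" per cent.

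No formula, expected event count, treated-arm risk or sidedness is given. Sections 4.6 and 14 place the cardiovascular results in supplementary material because of the low power, and Section 11 treats all outcomes as exploratory.

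**The concern.** Power for a time-to-event comparison depends on the total number of events. If the placebo arm has a 29% risk and the other arm has 0.70 times the hazard, the other arm must have a lower risk than 29%. Applying 29% to everyone counts events that the assumed effect would have prevented. It therefore uses the treatment effect in the effect-size term and ignores it in the event count.

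What is at stake is the accuracy of figures that the plan publishes to help readers interpret the results. Section 14 also refers to a 10-year follow-up using similar methodology. If the same event rule were carried over, events would again be overcounted.

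**Working it through.** **Inputs.** Alpha 0.001 and group sizes are from Section 4. Placebo-group risks of 29%, 12.5% and 3.8% and a hazard ratio of 0.70 are from Sections 4.4 to 4.6.

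**Sidedness.** This is not stated, so it was inferred from the questionnaire figures. For the SF-36 the plan says "we will have a power of 83.0% to confirm or reject a 4-point increase on the SF-36". A two-sided t-test at 0.001 with difference 4 gives:
- SD 9.5: 83.0% (206 per arm) and 56.3% (137 per arm)
- SD 9: 88.3% and 63.7%

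All four agree with Sections 4.1 to 4.3 to the decimal. One-sided testing gives 87.7%, 64.2%, 91.8% and 71.1%. Two-sided alpha is therefore used below.

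**Formula (Schoenfeld, 1:1 allocation).** Power = Φ(√(D/4) × |ln 0.70| − 3.2905), where D is the number of events and |ln 0.70| = 0.3567.

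**Step 1: reproduce the stated figures, using D = total N × placebo risk.**
- Section 4.4, metformin: D = 412 × 0.29 = 119.5; Φ(1.949 − 3.2905) = 8.99% (stated 9.0%)
- Section 4.4, insulin pair: D = 274 × 0.29 = 79.5; Φ(1.590 − 3.2905) = 4.45% (stated 4.5%)
- Section 4.5, metformin: D = 412 × 0.125 = 51.5; 2.22% (stated 2%)
- Section 4.5, insulin pair: D = 274 × 0.125 = 34.2; 1.23% (stated 1.2%)

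One rule fits all four to rounding or within about 0.05 of a percentage point.

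**Step 2: try other explanations for Section 4.4.**
- One-sided testing with events consistent with the hazard ratio: 10.1% and 5.4%
- Two-sided two-proportion test with a risk ratio of 0.70: 10.6% and 5.2%

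Neither fits.

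**Step 3: apply the plan's inputs as written.** Under proportional hazards, the other arm's risk is 1 − (1 − p)^0.7, and D = n per arm × (p + that risk).

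| Section | Placebo risk | Other-arm risk | Events (metformin / insulin pair) | Power | Stated |
|---|---|---|---|---|---|
| 4.4 | 29% | 21.3% | 103.7 / 68.9 | 7.0% / 3.5% | 9.0% / 4.5% |
| 4.5 | 12.5% | 8.9% | 44.1 / 29.4 | 1.8% / 1.0% | 2% / 1.2% |
| 4.6 | 3.8% | 2.7% | 13.3 / 8.9 | 0.4% / 0.3% | almost 0% / 0% |

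For example, 206 × (0.29 + 0.2132) = 103.7, and Φ(1.816 − 3.2905) = 7.0%.

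**Step 4: check that the result does not hang on one approximation.** For Section 4.4, Freedman's formula gives 6.8% and 3.4%, and a log-rank simulation (60,000 trials per case) gives 6.9% and 3.1%. For the Section 4.5 insulin pairs the simulation gives 0.8%, also below 1.2%.

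**The case against.** **The mechanism is inferred.** The article shows no event count or formula. This is true, and the wording of the point must reflect it. It does not rescue the figures: whatever route produced them, 9.0% and 4.5% do not follow from 29% in the placebo group, a hazard ratio of 0.70 and two-sided alpha 0.001.

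**The differences are small beside the uncertainty of the inputs.** With events counted correctly, a placebo risk of about 33% instead of 29% would give close to 9%. The 29% comes from a cited source, and its time horizon is not stated. This stands as a reason to grade the point as minor. It does not make the stated figure right for the stated input.

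**Nothing in the plan turns on it.** Recruitment ended at 412, and the figures are used only to argue that power is too low. This stands in full.

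**Stronger readings that the documents do not support.**
- A reader might infer that all six figures are wrong in the favourable direction. They are not. The 2% in Section 4.5 is 1.8%, which rounds to 2%. In Section 4.6, almost 0% and 0% are fair rounding of 0.4% and 0.3%, and they err low.
- A reader might call 0% impossible because power should not fall below alpha. That treats rounding to a whole number as a logical error. With so few events the lower bound is also unreliable: the simulation for cardiovascular death gave about 0.2% and 0.05%.
- A reader might infer that the plan presents the cardiovascular outcomes as better supported than they are. It does the opposite: Section 14 says the data are insufficient for realistic effects.

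**Conclusion.** The point holds as a minor numerical error. In Section 4.4 the stated powers exceed what the plan's own inputs give by about 2.0 percentage points (9.0% against 7.0%) and 1.0 point (4.5% against 3.5%). The implied event count is too high by about 15% (119.5/103.7 = 1.15). In Section 4.5 only the insulin-pair figure is affected, by 0.2 points (1.2% against 1.0%). The remaining three figures stand at the precision given.

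This rests on two-sided testing (inferred from the questionnaire figures), proportional hazards (the plan's Cox model), equal arms of 206 or 137, and no loss of events, in line with Section 7. For the insulin pairs it also rests on using the placebo-group risk for the reference regimen. That is an assumption, since neither arm of an insulin pair is a placebo group.

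The exploratory status and supplementary reporting do not change. The lower power only reinforces them.

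**What to change.** - Section 4.4: restate 9.0% and 4.5% as about 7.0% and 3.5%, with about 104 and 69 expected events.
- Section 4.5: restate 1.2% as about 1.0% (about 29 expected events). Keep 2% (about 44 events).
- Section 4.6: leave the figures as they are. Expected events of about 13 and 9 could be added.
- State once that the power figures are two-sided and that events are counted as n per arm × (p + 1 − (1 − p)^0.7).
- Describe the risk used for the insulin pairs as an assumed risk on the reference regimen.

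The cost is three changed numbers and a sentence or two of text. No analysis, threshold or reporting decision is affected.
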